## Abstract

**Objectives:**

This manuscript (1) outlines the intervention, (2) describes how its effectiveness is being evaluated in a pragmatic randomized controlled trial, and (3) summarizes the embedded process evaluation aiming to understand key barriers and facilitators for implementation in new environments.

**Methods:**

Participating centers refer eligible individuals with COPD following discharge from their local PR program. Consenting patients are assigned to a year-long community exercise program or usual care using block randomization and stratifying for supplemental oxygen use. Patients in the intervention arm are asked to attend an exercise session at least twice per week at their local community facility where their progress is supervised by a case manager. Each exercise session includes a component of aerobic exercise, and activities designed to optimize balance, flexibility, and strength. All study participants will have access to routine follow-up appointments with their respiratory physician, and additional health care providers as part of their usual care. Assessments will be completed at baseline (post-PR), 6, and 12 months, and include measures of functional exercise capacity, quality of life, self-efficacy, and health care usage. Intervention effectiveness will be assessed by comparing functional exercise capacity between intervention and control groups. A mixed-methods process evaluation will be conducted to better understand intervention implementation, guided by Normalization Process Theory and the Consolidated Framework for Implementation Research.

**Results:**

Based on results from our pilot work, we anticipate a maintenance of exercise capacity and improved health-related quality of life in the intervention group, compared with a decline in exercise capacity in the usual care group.

**Discussion:**

Findings from this study will improve our understanding of the effectiveness of community-based exercise programs for maintaining benefits following PR in patients with COPD and provide information on how best to implement them. If effective, the intervention represents an opportunity to transition patients from institutionally-based rehabilitative management to community-based care. The results of the process evaluation will contribute to the science of translating evidence-based programs into regular practice.

## Introduction

### Background

Chronic obstructive pulmonary disease (COPD) is a leading cause of death across the world [1] and will become increasingly common with an aging population. The prevalence of COPD increases with age and is highest in individuals aged 65 years and over [2], with a current prevalence of 20% in this age group [3]. The natural course of COPD is that of progressive worsening of airflow limitation, repeated exacerbations, respiratory failure, and premature death. Among the major chronic illnesses in Canada, COPD accounts for the highest rate of hospital admissions [4]. Coupled with the knowledge that COPD is a common and costly condition [5], long-term strategies to improve health outcomes and prevent functional decline are likely to result in a decrease in health resource usage [6].

It is well established that pulmonary rehabilitation (PR) for those who suffer from COPD results in short-term improvements in dyspnea, exercise capacity, and health-related quality of life (HRQL). However, benefits achieved through PR tend to diminish over time [7,8], often to the point that outcomes return to preintervention levels within 12 months [9,10]. Nonadherence to a maintenance home exercise program is a key factor associated with the decline in outcomes [9,11], with a 50% reduction in adherence only 9 months after completion of intensive rehabilitation, according to patient self-report [11]. While patients are encouraged to adhere to their home exercise program upon discharge, many have difficulty maintaining their exercise routine after the transition from a hospital-based rehabilitation setting to a community setting. The benefit of rehabilitation is further diminished as patients who develop acute exacerbations struggle to return to their previous level of exercise without professional guidance [11].

Consequently, there is a growing interest in developing innovative follow-up strategies to promote long-term exercise maintenance. Supervised exercise programs delivered following PR appeal to individuals with COPD [12] and are more effective than usual care for preserving exercise capacity in the medium term [13] Studies that have examined post-rehabilitation maintenance programs in patients with COPD have not shown consistent positive effect [14,15]. The optimal method for preventing functional decline following PR remains unclear, especially in individuals with moderate and severe COPD who experience frequent exacerbations.

Data from a systematic review [13] suggests that maintenance programs with higher exercise frequency and those that involved health care support, particularly after exacerbations, provided the greatest benefit. These findings complement patient-reported barriers and facilitators from qualitative work, suggesting program proximity and a scheduled, group-based format supervised by an individual who could facilitate rapid access to a health care professional were key features to promote adherence to community-based programs [16]. The potential benefits of community-based programs extend beyond the exercise component to include opportunities for social interaction among individuals who face similar challenges in their day-to-day lives and potential follow-up for those who do not adhere. An important advantage of this type of model is the transfer of wellness maintenance away from a medical environment to a fully integrated community setting.

In light of these findings, we developed a post-PR community-based exercise maintenance program for patients with COPD and completed a pilot at a single community site. Results from our pilot study demonstrated the program was feasible and well-tolerated by participants [12]. In contrast with previous studies evaluating community-based programs post-PR, our pilot work noted sustained significant improvements in physical function and HRQL at both 6 months and 1 year following PR [17]. With the success of the pilot program, a randomized controlled trial is required to determine the effectiveness of this maintenance strategy. The overall aim of this study is to evaluate the effectiveness of a post-rehabilitation community-based exercise maintenance program that uses existing community resources to provide individuals with COPD the opportunity to exercise in a community rather than an institutional setting. This research has the potential to not only prevent functional decline in those with COPD but also to improve their HRQL. Specific objectives are below:

## Objectives

To evaluate the effects of a 1-year community-based maintenance exercise program on functional exercise capacity in individuals with moderate to severe COPD who have completed a course of PR.To determine the effects after 1 year of this intervention on secondary outcomes including HRQL, functional strength, self-reported functional status, adherence to exercise and self-efficacy.To conduct a process evaluation to understand how the intervention was operationalized at each site and to identify factors that facilitated or impeded the implementation process.

## Methods

### Study Design

The proposed study design is a two-arm, multicenter randomized controlled trial with blinding of both the outcome assessor and data analyst. A detailed participant flow chart can be found in Figure 1.

The protocol received ethics approval from the Joint Bridgepoint/West Park/Toronto Central Community Care Access Centre Research Ethics Board (REB); the Trillium Health Partners REB; the Lakeridge Health REB; the University Health Network REB; and the St. Joseph’s Care Group REB. The trial is registered with ClinicalTrials [NLM Identifier: NCT01942499].

**Figure 1 figure1:**
[figure not shown]
Participant flow chart (6MWT, six-minute walk test; CRDQ, chronic respiratory disease questionnaire; CSES, COPD self-efficacy scale; DASI, duke activity status index; HUI, health utility index; PR, pulmonary rehabilitation including all core components of exercise, education, self management and psychological support, in keeping with international guidelines).

### Setting

In the province of Ontario, many health care services are covered under the Ontario Health Insurance Program (OHIP), a government-run health plan that is publicly funded. OHIP covers medically necessary services provided by physicians, including basic and emergency services, specialist visits, and formal rehabilitation (which includes PR). Community-based exercise programs are not covered under OHIP, and can be found in both municipal and private facilities.

### Participants

Individuals with COPD will be considered eligible for the study if they: (1) have moderate to severe COPD based on international (GOLD) criteria [18], (2) are clinically stable as determined by their respirologist, (3) have completed PR within the previous 2 weeks, and (4) are able to provide their own informed consent. Participants will be given written study information for review and will completed a written consent form prior to study enrollment. All participants will be under the active care of a respirologist.

Individuals will be excluded if they have associated medical conditions that significantly limit their ability to exercise. Specifically, participants who report a history of significant cardiovascular disease (ie, congestive cardiac failure, history of cardiac arrest, acute myocardial infarction within the preceding 3 months, symptomatic ischaemic cardiac disease, or uncontrolled systemic hypertension) or report severe nonrespiratory symptoms during exercise will be excluded from the study. Participants receiving mechanical ventilation and those who are unable or unwilling to attend the community-based exercise program or follow-up assessment sessions will also be excluded.

### Allocation

A computer-generated randomization schedule using variable block size will be created. A member of the research team will consecutively randomize participants using sealed, opaque envelopes. Randomization will be stratified by the use of supplemental oxygen to minimize the impact of this factor, as it has been shown to influence the response to PR [19] and improve the total distance achieved during the 6-minute walk test (6MWT) by 12 to 59 m [20,21].

### Intervention

The course of PR completed by both groups is in accordance with international guidelines [8] and will consist of all core components of rehabilitation including exercise, education, self-management, and nutrition, as well as psychological support. Thus, all participants will possess the tools and knowledge necessary to manage their condition prior to enrolment in the community maintenance program. Post-PR, participants randomized to the intervention group will receive the community-based maintenance exercise program for 12 months.

#### Control: Usual Care

Patients in both groups will receive usual care by their family physician and respiratory specialist (ie, medical care or prescriptions will not be standardized). Post-PR, they will receive the standard home exercise instructions and regular appointments with a physical therapist to review their program and address any outstanding issues.

#### Intervention: Community-Based Exercise Program

The intervention group will receive the same usual care and follow-up as the control group. In addition, they will be enrolled in a community-based maintenance exercise program for 12 months. Participants will be asked to attend a minimum of two sessions per week and are able to attend more frequently if they so choose. Each session will be approximately 60 minutes in duration. The exercise program will be delivered at one of seven community centers affiliated with the study; location selection will be based on the patient’s preference and proximity to their home. Each participant will receive a full, 1-year membership to the community center as part of the study.

Group-based classes led by a certified fitness instructor will be offered at least twice per week, although participants will have the option of attending the community center at an alternative time if they are unable to attend the group class. Participants who attend the center outside of class times will have access to a certified fitness instructor for supervision. Fitness instructors will be certified by the Canadian Society for Exercise Physiology, the principal body for physical activity, health and fitness research, and personal training in Canada. Educational materials and training workshops regarding issues pertinent to supervising patients with COPD during exercise, symptom management, and guidelines for training progression will be provided to fitness instructors prior to launching the study.

The content of each exercise program will be individualized according to each participant’s specific needs. Each exercise session will include a component of aerobic exercise such as walking or cycling, upper-limb resistance exercise (eg, free weights for bicep curls and triceps extensions), and activities designed to optimize balance, flexibility and strength (eg, functional exercises such as minisquats, stairs, basic stretches, core strengthening) based on PR guidelines (see Table 1 for an example). In addition to attending the twice weekly exercise program, participants will be encouraged to continue with their home exercise program consisting of aerobic exercise and strengthening. As we expect an inherent degree of variability in program delivery across sites, individual program details will be evaluated and reported as part of the process evaluation in order to capture variation across sites.

**Table 1 table1:** Example of exercise program at community center.

Type	Approximate duration	Potential activities
Warm up	10 minutes	Gentle stretches for all major muscle groups (neck, shoulders, arms, hamstrings, quadriceps, and calves); marching on the spot to increase heart rate.
Aerobic training	20-30 minutes	Walking along a designated track with rests as needed, cycling and/or treadmill.
Functional exercises to promote strength and balance	20-30 minutes	Free weights and ‘wall climbing’ for upper extremity; mini-squats, stairs, hip abduction and hip extension while holding onto the back of a chair (therabands available to add resistance) for lower extremity; basic balance exercises such as practicing tandem stance, standing on one leg, walking on different surfaces (with mats and rails available for safety).
Cool down	10 minutes	Gentle stretches for all major muscle groups (neck, shoulders, arms, hams, quads, and calves); slow walking to decrease heart rate.

The case manager, a member of the research team and a clinically trained physiotherapist, will have training in pulmonary rehabilitation and be familiar with the rehabilitation programs offered at each site. The case manager will collaborate with the patient’s PR physiotherapist and community center fitness instructor to establish the initial frequency, intensity, and training modalities for the community exercise program, tailored to the individual’s capacity. During the 12-month community-based program, the case manager will remain in communication with participants and fitness staff via a study phone-line and email. Participants attending exercise classes will be asked to contact the case manager by telephone after an absence of more than 1 week, due to illness or other reasons, so that support may be provided in managing exacerbations and resuming regular exercise. If significant new health problems arise, participants will be encouraged to return to their family doctor or respiratory specialist for review. Preliminary results from our pilot study demonstrated that the case manager was only accessed on occasions where a patient required additional support in managing exacerbations and where the medical safety of the patient was unclear to the fitness instructor. Feedback from focus groups with participants indicated that the presence of a case manager was a valued component of the model [12]. The role of the case manager moves this model into an integrated care strategy by providing patients and fitness staff with access to a health care professional when needed.

## Outcomes

### Primary Outcome

#### Six-Minute Walk Test

The 6MWT is a valid, responsive, interpretable, self-paced test that quantifies functional exercise capacity in terms of the distance walked in 6 minutes (6-minute walk distance) in patients with COPD [22]. The test will be performed over a 30-m level, straight course within an enclosed corridor, using the protocol described by the American Thoracic Society [22]. Outcome assessors will receive standardized training and will be blinded to group allocation. The measurement properties of this test have been well established in the COPD population [23]. A minimum important difference (MID) for the 6MWT is 54 m [24].

### Secondary Outcomes

#### Chronic Respiratory Disease Questionnaire

Health-related quality of life will be measured using the Chronic Reparatory Disease Questionnaire (CRQ). The CRQ is a disease-specific instrument evaluating four domains that are considered important to individuals with chronic airflow limitation [25,26]. Participants will be required to quantify events and experiences that have taken place over the 2-week period preceding administration of the questionnaire. It includes 20 questions in four domains: dyspnea, fatigue, emotional function, and mastery. Answers are scored on a 7-point scale ranging from 1 (maximum impairment) to 7 (no impairment). The results are expressed as the mean score for each domain and the mean overall score. The MID for the CRQ is a change (improvement or deterioration) of 0.5 per item [27]. The CRQ is valid, responsive and interpretable when used among patients with COPD [25-27].

#### Duke Activity Status Index

The Duke Activity Status Index (DASI) is a 12-item questionnaire that requires only simple yes/no responses and takes less than 5 minutes to complete [28]. The questionnaire includes activities representative of personal care, ambulation, household tasks, sexual function, and recreational activities. The DASI has high criterion validity for predicting functional outcomes in patients with moderate to severe COPD [29] and was responsive to change in our pilot study [17].

#### Lower Extremity Functional Strength

The repeated chair stand test (number of sit-to-stands the subject can complete in a 30-second time-period) will be used as a measure of functional lower body strength. Reliability and validity of this measure has been previously evaluated in community-dwelling older adults [30] and in people with COPD [31] and it has been shown to be correlated to maximal voluntary force from a seated leg press [30,31].

#### Self-Efficacy

Behavioural modification is embedded in the rehabilitation process. Bandura describes the concept of self-efficacy as the ‘belief in one’s capabilities to organise and execute the course of action required to produce given attainments’ [32]. A specific self-efficacy scale has been designed and validated for COPD, the COPD self-efficacy scale (CSES) [33], and was recently shown to be responsive to the effects of PR [34]. It is a 34-item questionnaire divided into five sections, one of which pertains to exercise.

#### Exacerbations

Acute exacerbations will be defined based on symptoms according to the criteria described by Anthonisen and colleagues [35], which are increased dyspnea with changes in sputum purulence or volume lasting at least 2 consecutive days. We will use intervention-based criteria for classifying the exacerbation as mild, moderate, or severe, depending on whether they are managed at home with no additional health care contact (mild), at home with unscheduled health care contact or the initiation of oral corticosteroids or antibiotics (moderate), or in the emergency room or hospital (severe) [35]. Patients will be asked to self-report this information at each assessment.

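### Contact alone makes a home-managed exacerbation moderate, and only the intervention arm has a case manager to phone, so the mild/moderate split can differ by arm without any true difference

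*Protocol article*

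**What the plan says.** Under Secondary Outcomes, Exacerbations, an episode is identified by symptoms lasting at least two days. Its severity is then graded separately: "We will use intervention-based criteria for classifying the exacerbation as mild, moderate, or severe". An episode is mild if "managed at home with no additional health care contact (mild"). It is moderate if handled "at home with unscheduled health care contact or the initiation of oral corticosteroids or antibiotics (moderate"). Severe means emergency room or hospital. The source is the patient: "Patients will be asked to self-report this information at each assessment", and the abstract places assessments at baseline, 6 and 12 months.

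The section on the community-based exercise program describes the case manager: "The case manager, a member of the research team and a clinically trained physiotherapist, will have training in pulmonary rehabilitation". It then gives an instruction: "Participants attending exercise classes will be asked to contact the case manager by telephone after an absence of more than 1 week, due to illness". The same sentence also covers absence for other reasons, and gives help with exacerbations and with returning to exercise as the purpose. The section sums up the role as "providing patients and fitness staff with access to a health care professional when needed".

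The control section gives both arms usual care, with regular physical therapist appointments. The intervention arm receives this and the program on top. No case manager line is described for controls.

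**The concern.** A severity grade based on management is comparable between arms only if the management that triggers it is equally open to both. Here one trigger, unscheduled health care contact, has a route that the intervention itself supplies to one arm. Helping with exacerbations is a stated purpose of that route, so the artefact falls on an outcome that the program is meant to influence.

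The definition does not say whether a case manager call counts, and the information is self-reported. A patient who spoke to a physiotherapist about an exacerbation could reasonably report it as health care contact. A control patient with the same episode has no such call to report. The error is differential by arm, so a larger sample would not remove it. At stake is any table or statement comparing mild and moderate exacerbations between arms: the program could appear to have more moderate episodes, or a real benefit could be hidden.

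**Working it through.** The article gives no exacerbation rate or expected severity split, so there is no figure of its own to reproduce on this point. The check has two parts: comparing the definitions, then an illustration with assumed inputs.

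**Comparing the definitions.** Take one episode that meets the symptom criteria, is managed at home, has no oral corticosteroid or antibiotic, and involves no physician, emergency or hospital contact. Suppose it keeps the patient from the usual routine for more than a week.

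- Control arm: no additional contact, so mild.
- Intervention arm: the patient phones the case manager as asked. The article calls this person a health care professional, and the call was not a booked appointment. The episode no longer meets the mild criterion and, on the literal wording, meets the moderate one.

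Other episodes are graded alike in both arms under this mechanism. A corticosteroid or antibiotic course makes an episode at least moderate, and an emergency room visit or admission makes it severe, with or without a call. Whether an episode counts at all depends on symptoms, so the total is unchanged.

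**Illustration.** All inputs are assumptions; none is in the article. Both arms have identical true episodes. Let s = 0.15 be the severe share, m the truly mild share (0.30 or 0.50), and c the share of truly mild episodes in the intervention arm that lead to a counted call (0.10, 0.25 or 0.50).

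- Moderate share, control = 1 − m − s
- Moderate share, intervention = (1 − m − s) + m × c
- Spurious moderate ratio = 1 + c × m / (1 − m − s)
- Mild ratio, intervention to control = 1 − c

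| m | c | Moderate, control | Moderate, intervention | Moderate ratio | Mild ratio |
|---|---|---|---|---|---|
| 0.30 | 0.10 | 0.55 | 0.55 + 0.03 = 0.58 | 1.05 | 0.90 |
| 0.30 | 0.25 | 0.55 | 0.55 + 0.075 = 0.625 | 1.14 | 0.75 |
| 0.30 | 0.50 | 0.55 | 0.55 + 0.15 = 0.70 | 1.27 | 0.50 |
| 0.50 | 0.10 | 0.35 | 0.35 + 0.05 = 0.40 | 1.14 | 0.90 |
| 0.50 | 0.25 | 0.35 | 0.35 + 0.125 = 0.475 | 1.36 | 0.75 |
| 0.50 | 0.50 | 0.35 | 0.35 + 0.25 = 0.60 | 1.71 | 0.50 |

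The ratio depends only on c and on the ratio of mild to moderate episodes in control. As c approaches zero the ratio approaches 1, so the low end matters as much as the high end.

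**The case against.** There is a fair case that this matters little.

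- **The trigger is narrow.** The request to phone follows an absence of more than a week, whereas two days of symptoms make an exacerbation. Many mild episodes would prompt no call. This stands.
- **Calls may be rare.** The article reports that in the pilot the case manager was used only on occasion, when a patient needed extra support with an exacerbation or a fitness instructor was unsure about medical safety. Such episodes may often also involve drugs or a physician, and would then be moderate in either arm. This stands, and is why the low end of the range is shown.
- **No formal comparison is named.** Data Analysis omits exacerbations from its list of modelled outcomes and mentions them only as a baseline adjustment variable, which calls made after randomization cannot alter. This limits the point to descriptive reporting, but exacerbations are still listed as a secondary outcome and will presumably be reported by arm.
- **A call requested by the program might not be unscheduled health care contact.** The case manager is also a member of the research team, so this reading is possible. It does not settle the matter: the mild category requires no additional contact, so a call that is additional but not unscheduled would fit neither category. The wording needs resolving on either reading.

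A reader might go further and infer that the comparison is set up to make the program look worse, that calls sharpen recall in one arm, or that asking about contacts unblinds the assessor before the walk test. The article supports none of these. It plans no formal severity test, says nothing about recall, and does not say who asks these questions or in what order. It does state that outcome assessors are blinded. Visit order and question scripts are details that a condensed article may leave to the full protocol.

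**Conclusion.** The point holds in a limited form. As written, the definition can grade the same drug-free, home-managed episode as moderate in the intervention arm and mild in control, because contact alone is sufficient, one arm has an added contact route, and nothing excludes it. Any between-arm description of the mild/moderate split is then biased against the program.

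The size cannot be determined from the article and may be small. With 10% to 50% of truly mild episodes leading to a counted call, 30% to 50% of episodes truly mild and 15% severe, the spurious moderate ratio runs from about 1.05 to 1.7, and mild episodes fall by 10% to 50%. These inputs are assumed, and the result also requires that patients report the calls as health care contact. The total exacerbation count, drug-treated episodes, the severe category and the primary 6-minute walk result are not affected.

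**What to change.** Add one sentence to the exacerbation definition: contact with the study case manager or a fitness instructor does not count as health care contact when severity is graded. Apply it identically in both arms. Alternatively, report between-arm severity only on initiation of oral corticosteroids or antibiotics and on emergency room or hospital use, so that contact alone no longer decides the grade.

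The exclusion leaves real physician visits in the grade, including any that follow from the program's encouragement to see a doctor about significant new health problems. Those are actual health care use and can be reported as such.

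The cost is a wording change and no new procedure. The downside is retrospective: the article says about half the participants are enrolled, so episodes already graded moderate on contact alone need re-checking to see whether the contact was with study staff. For older self-reports this may not always be recoverable, in which case the alternative is the safer basis for comparison, provided drug and hospital use were recorded separately.
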